### Modification or discontinuation of study interventions

A primary intervention approach is endorsed during the PAT-A anxiety formulation; however, this may be modified in light of new information and progress during therapy. To ensure that the intervention can be implemented, specific components of another module will be considered within the context of a developing formulation during therapy supervision between the therapist and clinical supervisor. When an entirely different intervention module is indicated (a deviation from the original PAT-A formulation), a consultation group, consisting of members of the trial team, will be convened. The recommendations of the consultation group will be recorded, although treatment decisions remain with the therapist and clinical supervisor.

Participants will be entitled to discontinue their treatment at any time and without having to give reason. Interventions may also be discontinued when both the therapist (in consultation with the clinical supervisor) and participant agree that continuing with therapy is unlikely to be beneficial due to factors such as concurrent life events, participant motivation, session attendance and engagement. Treatment will be discontinued if a screening error becomes apparent during treatment, e.g. the identification of a clinical presentation that meets the exclusion criteria or if a significant or immediate clinical risk is identified, and continuation of PAT-A would be contraindicated. Such decisions will be made through clinical supervision and in consultation with the participant. In any such eventuality, the trial therapist will ensure that the participant is referred to an appropriate service for ongoing clinical support.

### Adverse event recording

Any adverse event (defined within the trial as unexpected events) will be recorded using a pre-existing checklist [67]. Events to be recorded include deterioration of existing symptoms, the emergence of new symptoms, significant changes in life circumstances and strains in family relationships. All adverse events will be discussed in supervision and the Trial Management Group for those defined as significant will be dealt in accordance with relevant NHS protocols and reported to the sponsoring NHS Trust and the reviewing Regional Ethics Committee as per the standard operating procedure of the sponsoring NHS Trust. All adverse events will be recorded and filed in the Trial Management File (TMF). Any significant adverse events that occur as a result of the trial intervention(s) will be reported in any publications and the same may be true for an adverse event that was not caused by study interventions but likely had a significant impact on a participant’s capacity to engage successfully with trial interventions.

The trial has been indemnified by Newcastle University and Cumbria, Northumberland, Tyne and Wear NHS Foundation Trust. It is not expected that participants will experience any significant harm as a result of taking part in this trial. Should any participant experience significant harm then this would be reported to the sponsoring trust, which would manage this through their standard procedures.

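### The adverse event definition (unexpected events) conflicts with the list of events to be recorded, and the firm publication commitment covers only significant events attributed to the intervention, so no by-arm harms report is committed

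*Protocol article*

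**What the plan says.** All the relevant text is in the protocol article, Methods/design, Adverse event recording.

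- Definition and tool: "Any adverse event (defined within the trial as unexpected events) will be recorded using a pre-existing checklist".
- Scope: "Events to be recorded include deterioration of existing symptoms, the emergence of new symptoms, significant changes in life circumstances and strains in family relationships".
- Review: "All adverse events will be discussed in supervision and the Trial Management Group". The section also says that every adverse event is recorded and kept in the trial's management file.
- Publication, firm part: "Any significant adverse events that occur as a result of the trial intervention(s) will be reported in any publications".
- Publication, discretionary part: "the same may be true for an adverse event that was not caused by study interventions", limited to events that probably had a significant effect on the participant's capacity to engage with the trial interventions.

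Elsewhere, Randomisation says that participants cannot be blinded and that a trial therapist tells them their allocation. Data collection and management says that there will be no data monitoring committee.

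**The concern.** There are two separate faults, and both lie in rules that the article states, not in detail that it leaves out.

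First, expectedness is made a condition for being an adverse event at all. It is normally a label given to an event after it has been captured. Here the person recording has to judge whether a worsening was to be expected before deciding whether it counts, and the list that follows points the other way.

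Second, the firm commitment to publish depends on attribution. Some participants with an anxiety disorder will get worse under any care. The rate at which this happens in the control arm is the background against which events in the PAT-A arm have to be read. A rule that publishes mainly what is judged to be caused by treatment can leave that background out.

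The pilot is meant to inform an application for a fully powered trial (Discussion, Significance). An unclear definition and a selective harms report could both carry over into that trial.

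**Working it through.** The section states no rate, target or sample size for harms, so there is no figure to reproduce and no arithmetic applies. The check is to set the sentences side by side and follow typical events through them.

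**Step 1: definition against list.** The two sentences can be read in two ways.

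- *The definition governs.* The list then illustrates kinds of unexpected event, and worsening counts only if it was unexpected.
- *The list governs.* Any worsening of existing symptoms is recorded.

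The readings differ for foreseeable worsening, and that category is not empty. Participants must have clinically significant anxiety (Recruitment and eligibility criteria). The package includes graded exposure in virtual reality environments (Abstract, Methods/design), and the Mindfulness module is meant in part to help people engage with situations that provoke anxiety (Study interventions). The promise to record and file all adverse events does not settle the matter, because it uses the term as defined.

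**Step 2: what is committed to publication.** The firm rule needs significance and causation together. The discretionary rule needs no causation but a probable effect on engagement, and even then says only *may*.

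| Event | Counts if definition governs | Counts if list governs | Publication |
|---|---|---|---|
| Significant, unforeseen, attributed to the intervention | Yes | Yes | Firmly committed |
| Foreseeable worsening of anxiety during exposure work | No | Yes | Committed only if it counts, is significant and is attributed |
| Attributed to the intervention but not significant | If unexpected | If of a listed kind | No commitment |
| Significant, not attributed, probably impaired engagement | If unexpected | If of a listed kind | *May* be published |
| Significant, not attributed, engagement not affected | If unexpected | If of a listed kind | No commitment |

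**Step 3: by arm.** The firm rule speaks of trial interventions in general, so a significant event caused by the two control sessions would be covered. Deterioration under the usual care that follows those sessions would seldom be attributed to them, and would seldom be said to have impaired engagement with them. It would therefore tend to fall in the last row. Nothing in the section promises a count of all adverse events by arm.

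**The case against.** The strongest case on the other side has four parts.

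*Worsening is captured elsewhere.* It is named for recording. Worsening is also rated in both arms at 3 months after the intervention: by the blinded research associate on the CGI-I (6 and 7 count as worsening) and by a blinded panel on the 9-point target-situation scale (6 to 9 are worse). The ASA-A is repeated, and the interview asks about negative change. This stands, and it rules out a reading that tempts: that expected worsening is missed. The text supports only that it may be left out of the adverse event record. The other measures are not a full substitute. They compare baseline with 3 months after the intervention, so worsening that arises in treatment and then resolves can escape them, as can events in people not followed up. The interview is an offer, not a requirement.

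*Serious harm would meet the definition anyway.* The section says that significant harm is not expected, so such harm would be unexpected and would count. This also stands. The definitional fault is confined to foreseeable worsening.

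*Ascertainment may be specified in the full protocol.* A reader might infer that events come to light through supervision, or mainly at therapy sessions, so that up to 12 sessions in one arm against two in the other would distort the comparison. The text does not say this. Events go on a checklist, and supervision and the Trial Management Group are where they are discussed. Who completes the checklist, and when, is not stated, and an article may leave that to the full protocol. A reader might likewise infer that unblinded staff judge causality, but the article does not say who judges.

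*Nothing forbids fuller reporting.* All recorded events are filed and could be tabulated by arm, and comparing harms is not among the main feasibility outcomes. This stands as far as it goes. It means that the harms data need not be uninterpretable, but a possible tabulation is not a committed one.

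**Conclusion.** The point holds in two parts. The definition and the list conflict over foreseeable worsening and must be reconciled. The firm publication rule is limited to events that are significant and attributed to the intervention, which leaves no committed by-arm harms report and leaves events in the control arm especially likely to go unpublished.

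The effect is on which events are counted and which are reported. It cannot be given a number or a direction from this document. The first part assumes that some worsening of anxiety is foreseeable in this therapy, which follows from the population and from the exposure work. The second assumes only that the publication sentences are followed as written. Neither part depends on how the checklist is administered.

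**What to change.** 1. Remove *unexpected* from the definition. Define an adverse event irrespective of whether it was expected or is thought to be related to the intervention, so that the definition and the list agree.
2. Record expectedness and relatedness as separate fields for each event.
3. Replace the publication rule with a commitment to report all recorded adverse events by arm, regardless of attribution, and state how events were ascertained in each arm. If the full protocol already describes the ascertainment, a cross-reference is enough.

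The cost is revised wording, two fields on the record and a longer adverse event table. The trial was still recruiting when the article was submitted, so the definition could be changed for the remaining participants, with the date of change reported. The reporting rule could be applied to all participants, since recorded events are already filed.

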### Statistical analysis

As this is a feasibility and acceptability pilot study, analyses will be mainly descriptive. Formal power calculations are not appropriate as the study is not designed to test for a difference between treatments. Feasibility will, therefore, be explored by examining:
The number of expression-of-interest forms received, the number who go on to consent and those who either choose not to take part (including reasons given) and those who are ruled out on eligibility groundsTake-up, attendance and engagement with the PAT-A© intervention and CCSPCompletion of follow-up data at 3 months and 12 months post interventionQualitative data regarding the acceptability of PAT-A© from the participants’ perspective

We will also undertake some preliminary analysis of treatment effects, and follow a pre-existing statistical analysis plan. The difference in mean change as assessed by the main outcome measure from our previous trials (‘target-situation’ vignettes) and anxiety screening tools will be examined between the groups from baseline to 3 months post intervention with accompanying 95% confidence intervals. Results will be interpreted cautiously because of the size of the study, the possible imbalance in pre-randomisation baseline covariates and the range of interventions offered to participants within the CCSP arm of the trial (Fig. 3).

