### Sample size

This pilot feasibility trial is not powered to estimate a target difference in relative effectiveness, but rather to address feasibility and acceptability of delivering an individualised anxiety treatment package for autistic adults with a variety of anxiety presentations to inform a future definitive trial. We aim to recruit up to 40 participants. This number is based on recommendations for good practice in feasibility studies [41].

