### Other outcomes

As the PAT-A© intervention has been developed to improve engagement with the specific target situations, the target situation rating will also be considered as an outcome measure to identify symptom change over time. As previously described two target situation vignettes will be developed in collaboration with the participant using baseline assessment data. Both vignettes and the severity of difficulties within the target situation are then reassessed 3 months post intervention by the RA. Degree of improvement will be rated by an expert panel of researchers and clinicians, blinded to the treatment group, which will compare the anonymised vignettes from baseline and follow-up and identify whether there has been any change since baseline. A 9-point scale (from 1 ‘normalised’, 2 ‘markedly improved’, 3 ‘definitely improved’, 4 ‘equivocally improved’, 5 ‘no change’, 6 ‘equivocally worse’, 7 ‘definitely worse’, 8 ‘markedly worse’ to 9 ‘disastrously worse’) will be used to rate change between baseline and 3 months post intervention. Comparisons of change scores for the two vignettes between the two groups across time (baseline to 3- month follow-up) will then be made. The research team also plans to repeat the target-situation interview and ratings at 12 months post intervention.

In addition to the target situations, the following questionnaire data will be collected at 3 months post intervention to allow analysis of differences between baseline and follow-up across the intervention and control groups:
• Anxiety: assessed using the full-scale score on the ASA-A• Quality of life: assessed using full-scale score and subscale scores on the WHOQoL-BREF plus the ASQoL and disabilities module• Health-related quality of life: assessed using full-scale score on the EQ-5D

The Clinical Global Impression of Improvement (CGI-I) will be used to assess global clinical change between baseline and 3 months post intervention. The CGI-I is a standardised framework for clinicians to assess to what extent participants’ symptoms have improved or worsened using a 7-point scale (1 – very much improved; 2 – much improved; 3 – minimally improved; 4 – no change; 5 – minimally worse; 6 – much worse; or 7 – very much worse). The RA, who is blind to group and clinically trained, will rate global improvement using all available data from baseline and 3-month post-intervention follow-up, including:

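### The anxiety questionnaire (ASA-A) is to be compared by difference in mean change; adjusting for its baseline would be more precise and would remove the over-correction of a chance baseline gap

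*Protocol article*

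**What the plan says.** All references are to the protocol article.

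- **Status of the analysis.** Statistical analysis describes the study as mainly descriptive, then adds: "We will also undertake some preliminary analysis of treatment effects, and follow a pre-existing statistical analysis plan". That plan is not at hand.
- **Estimator.** The same section names "The difference in mean change as assessed by the main outcome measure from our previous trials", meaning the target-situation vignettes, and continues that these and "anxiety screening tools will be examined between the groups from baseline to 3 months post intervention", "with accompanying 95% confidence intervals". No baseline covariate is mentioned.
- **Baseline imbalance.** The section foresees "the possible imbalance in pre-randomisation baseline covariates" and gives it as a reason to interpret results cautiously. It names no analytic response.
- **Size and allocation.** Sample size: "We aim to recruit up to 40 participants". Randomisation describes a simple schedule, with neither blocks nor strata.
- **The questionnaire concerned.** Baseline characterisation lists the ASA-A among the baseline self-report measures and gives a 1-month test-retest reliability of .823. Other outcomes makes the ASA-A full-scale score the anxiety questionnaire at 3 months post intervention.
- **The vignettes.** Under Other outcomes, a blinded panel compares baseline and follow-up vignettes, and a 9-point scale "will be used to rate change between baseline and 3 months post intervention". The section then promises "Comparisons of change scores for the two vignettes between the two groups across time".

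**The concern.** With at most 40 people and no stratification, the arms may well differ by chance on baseline ASA-A. A change score subtracts the whole of each person's baseline value. Unless the regression of follow-up on baseline has slope 1, that is too much: the arm that starts higher by chance is expected to fall further through regression to the mean, and part of that fall is counted as treatment effect. Subtracting the whole baseline also adds noise that a fitted slope would avoid.

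The article sees the imbalance coming and already collects the variable that would deal with it, yet its only stated response is caution in interpretation. At stake are the size and width of the preliminary ASA-A estimate. No test, power calculation or primary outcome depends on it. Aims and objectives does say that these outcomes are measured to inform the design of a later trial, so a cleaner estimate is worth having.

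**Working it through.** There is no stated figure to reproduce: the sample size rests on good-practice recommendations, with no effect size, SD or power. The check compares two estimators for a measure with a true baseline.

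**Inputs**
- N = 40 (Sample size). A 20:20 split is an assumption.
- rho, the correlation between baseline and 3-month ASA-A: not given. An assumed range of 0.3 to 0.823 is used. The top value is the 1-month retest figure, an upper guide because follow-up comes later and after treatment.
- Equal SDs at both times (assumption). Results are in SD units.

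**Shift from a chance baseline gap d**

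The expected change-score estimate, given d, is the true effect − (1 − rho)·d.

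- The SD of d is √(2/20) = 0.316, so |d| exceeds 0.3 SD with probability about 34% and 0.5 SD with probability about 11%.
- A one-standard-error gap at rho = 0.5 gives 0.316 × 0.5 = 0.158, about 0.16 SD.
- At rho = 0.823 it gives 0.316 × 0.177 = 0.056, about 0.06 SD.

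**Precision, n = 20 per arm**

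- Change score: variance = 2(1 − rho) × 2/n.
- Baseline-adjusted: variance = (1 − rho²) × 2/n × [1 + 1/(N − 4)], where the bracket is the cost of estimating the slope.
- Large-sample ratio, adjusted to change: (1 − rho²) / [2(1 − rho)] = (1 + rho)/2.
- The 95% half-width is the t quantile (38 df for change, 37 df for adjusted) times the square root of the variance.

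| rho | Half-width, change | Half-width, adjusted | Narrower by | (1 + rho)/2 |
|---|---|---|---|---|
| 0.3 | 0.757 | 0.620 | 18% | 0.65 |
| 0.5 | 0.640 | 0.563 | 12% | 0.75 |
| 0.7 | 0.496 | 0.464 | 6% | 0.85 |
| 0.823 | 0.381 | 0.369 | 3% | 0.91 |

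A comparison of 3-month scores that ignores baseline has half-width 0.640 at any rho. At rho = 0.5 the change score therefore gains nothing over ignoring baseline, and at 0.3 it is worse.

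**Checks**
- Simulation (20 per arm, 20,000 runs per value) gave variance ratios of 0.77, 0.87 and 0.94 at rho = 0.5, 0.7 and 0.823. These match (1 + rho)/2 times 37/36.
- With 16 per arm the intervals are narrower by 17.8%, 11.7%, 6.0% and 2.7% at rho = 0.3, 0.5, 0.7 and 0.823.
- The slope cost cancels the gain when (1 + rho)/2 × 37/36 = 1, that is, at rho = 72/37 − 1 = 0.946, above any value considered plausible here.

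**The case against.** **The estimator is valid, and little rests on it.** A change-score comparison is unbiased over randomisation. The primary outcomes are feasibility and acceptability, the effect analysis is called preliminary, and the article already urges caution. All of this stands, and it keeps the point minor.

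**The unseen analysis plan may adjust for baseline.** It may. The phrase does not strictly exclude an adjusted difference, since regressing change on group and baseline gives the same group difference as regressing the 3-month score on them. But the article does name an estimator, its plain reading is unadjusted, and caution is the only response it gives to imbalance. If the plan adjusts, the article's sentence should say so.

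**The gain may be small.** At .823, the only correlation-type figure in the article, the interval narrows by just 3%. That is fair, although a longer interval with treatment in between makes a lower correlation likely.

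A reader might also infer more than the text supports:

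- *That baseline imbalance is left uncorrected.* A change score does subtract the outcome's own baseline; the fault is over-correction. Only imbalance in other covariates goes unadjusted.
- *That the vignette rating is treated as though it had a baseline value.* Mean change as assessed by the vignettes reads naturally as the mean of the 9-point change rating, and baseline to 3 months as the interval it covers. No passage subtracts a baseline rating.
- *That two vignettes per person will make the intervals too narrow.* This would follow only if they were entered as independent observations, which the article does not say. How they are combined is a matter for the analysis plan.
- *That WHOQOL-BREF and EQ-5D are tied to the same estimator.* The sentence names only the vignettes and the anxiety tools. Other outcomes fixes no estimator for the quality-of-life measures.

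**Conclusion.** The point holds for the ASA-A. The stated difference in mean change is valid on average, but it over-corrects a chance baseline gap and is less precise than adjusting for baseline. A one-standard-error gap moves it by about 0.06 SD (rho = 0.823) to 0.16 SD (rho = 0.5), and the adjusted interval is 3% to 18% narrower as rho falls from 0.823 to 0.3.

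These sizes assume 20 per arm, equal SDs at the two times and a correlation within the assumed range. Reading the ASA-A as the anxiety tool meant in Statistical analysis follows from Other outcomes, where it is the anxiety questionnaire named for 3 months.

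This is a free improvement to a secondary, preliminary analysis and does not invalidate the plan. It does not reach the target-situation rating, which has no baseline on its own scale, so no such gain exists there; the shared wording is an ambiguity to clear up and not a demonstrated error.

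**What to change.** 1. **ASA-A.** In Statistical analysis, replace difference in mean change with the group difference at 3 months from a linear model containing group and baseline ASA-A, with its 95% confidence interval. The same model can serve any other questionnaire with a baseline if it is compared between arms.
2. **Target situations (wording only).** State separately that the 9-point rating is compared between arms as a 3-month rating, with one score per participant, for example the mean over the two vignettes.
3. **Consistency.** If the existing analysis plan already specifies this, bring the article's sentence into line with it.

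The cost is one degree of freedom in the ASA-A model and a few sentences of text. No new data are needed, because the ASA-A is already collected at both times.
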